## Abstract

**Background::**

For a long time, postoperative nutritional support for laryngeal cancer patients has depended on the gastric tube for enteral nutrition. Silica gel gastric tube is often used in clinical practice; however, the gastric tube placed in the conventional depth often leads to various complications in the stomach, thus damaging the nutritional status of patients and leading to the poor prognosis.

**Methods/design::**

A total of 80 patients with laryngeal cancer in otolaryngology, head and neck surgery department of Deyang people's hospital from May 2020 to April 2022 will be selected and randomly divided into control group and experimental group according to the numerical table. Patients in the control group will receive conventional gastric tube placement, with a depth of 45 to 55 cm, which can extract gastric juice. B-ultrasound accurately positioned the gastric tube in the stomach instead of the cardia, and postoperative nasal feeding nutrition will be provided. In the experimental group, the gastric tube will be pulled out 10 cm after conventional placement and no gastric juice will be extracted. B-ultrasonography verified that the gastric tube will be located below the esophagus or above the cardia, and routine nasal feeding will be performed postoperatively. Analysis for comfort and prognosis were performed by general comfort questionnaire and various index including height, body mass index, albumin value, electrolyte, wound healing, pharyngeal fistula.

**Discussion::**

In this study, visual simulation scale and general comfort questionnaire developed by Kolaba, an American comfort nursing specialist, were used to evaluate the comfort level of the 2 groups of patients, including pain, acid reflux, upper abdominal burning sensation, and hiccup. Objective indexes such as height, body mass index, albumin value, electrolyte, wound healing, and pharyngeal fistula were used to evaluate the prognosis of the 2 groups of patients. The visual simulation scale can preliminarily judge the subjective feelings of patients.

**Trial registration::**

It has been registered at http://www.chictr.org.cn/listbycreater.aspx (Identifier: ChiCTR2000030378), Registered February 29, 2020.

## Introduction

1

Laryngeal cancer is a common malignant tumor in otolaryngology head and neck surgery. All patients undergoing laryngeal cancer surgery need tracheotomy; however, the postoperative recovery process is slow. Indwelling of nasal feeding tube and tracheostomy have a great impact on the quality of life of patients.^[1]^ In terms of clinical status, more than 500 cases of laryngeal cancer operations were performed in our department from January 2012 to December 2020, and most of the patients complained of chest and anterior cardiac discomfort, acid reflux, burp, and gas discomfort, which brought huge psychological pressure and physical pain to patients. Comfort care is a holistic, individualized, creative and effective nursing mode, which can make people achieve pleasure in both physiology and psychology, thus reducing the society burden.^[2]^ The change of comfort level of patients with nasal feeding is the main reason for patients’ self-extubation.^[3]^ Therefore, it is particularly urgent to conduct clinical research on the selection of reasonable gastric tube placement depth for patients with laryngeal cancer. According to the clinical practice in our department, we found that most patients have significantly reduced discomfort after 10 cm of gastric tube is removed. To verify the rationality of this method, we plan to conduct a randomized controlled trial protocol in the present study.

## Methods/design

2

### Research object

2.1

We aim to explore the optimal depth of gastric tube placement in perioperative period for laryngeal cancer patients.

We aim to compare and analyze the differences in postoperative comfort and prognosis between the traditional gastric tube placement method (control group) and the modified lower esophageal gastric tube placement method (experimental group).

### Study method

2.2

A total of 80 patients with laryngeal cancer in otolaryngology, head and neck surgery department of Deyang people's hospital from May 2020 to April 2022 will be selected and randomly divided into control group and experimental group according to the numerical table. Analysis for comfort and prognosis were performed by general comfort questionnaire (GCQ)^[4]^ and various index including height, body mass index, albumin value, electrolyte, wound healing, pharyngeal fistula. By statistical analysis, the effects of 2 different gastric tube placement depths on comfort and nutritional status of laryngeal cancer patients will be evaluated.

### Participants

2.3

Inclusion criteria include the following:

(1)Eighty cases of laryngeal cancer surgery patients in otolaryngology head and neck surgery from March 2020 to September 2020 will enroll in this study.(2)Patients who deny a previous history of digestive disease will enroll in this study.(3)Patients who have normal cognitive, behavioral and communication skills will enroll in this study.(4)Patients who volunteer to participate in this study and sign the informed consent will enroll in this study.

Exclusion criteria include the following:

(1)Patients with hypopharyngeal cancer who have undergone chemoradiotherapy will be excluded;(2)Laryngeal cancer patients with serious internal and surgical diseases, such as hyperthyroidism, hypertension, heart disease, hepatitis will be excluded;(3)Illiteracy will be excluded.

### Interventions

2.4

Patients in the control group will receive conventional gastric tube placement, with a depth of 45 to 55 cm, which can extract gastric juice. B-ultrasound accurately positioned the gastric tube in the stomach instead of the cardia, and postoperative nasal feeding nutrition will be provided. In the experimental group, the gastric tube will be pulled out 10 cm after conventional placement and no gastric juice will be extracted. B-ultrasonography verified that the gastric tube will be located below the esophagus or above the cardia, and routine nasal feeding will be performed postoperatively.

### Measurement of outcomes

2.5

Tools to measure primary indicators include the following:

(1)The incidence of gastric complications.(2)In this study, visual simulation scale and GCQ developed by Kolaba,^[4]^ an American comfort nursing specialist, will be used to evaluate the comfort level of the 2 groups of patients, including pain, acid reflux, upper abdominal burning sensation, and hiccup.(3)Objective indexes such as height, body mass index, albumin value, electrolyte, wound healing, and pharyngeal fistula will be used to evaluate the prognosis of the 2 groups of patients.

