### Statistical analysis

2.6

Statistical analyses will be implemented by SPSS 17.0 and Microsoft Excel 2007 software. Data will be represented as mean ± standard deviation. A *t* test will be performed to compare the changes in measures within groups. Statistical significance will be considered at *P* < .05.

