## Discussion

3

Laryngeal cancer is a common malignant tumor in otolaryngology, head and neck surgery in China.^[5]^ Throat excision is the main treatment for laryngeal cancer patients. After surgery, patients need the indwelling gastric tube nasogastric feeding to obtain the nutrition required^[6]^; however, gastric tube indwelling for a long time can cause a series of complications, such as gastric retention, diarrhea, hiccups, nasogastric tube, aspiration, and pharyngeal fistula.^[7]^ In addition, indwelling nasogastric feeding tube can also make the patient appear acid reflux, sternal pain, stomach burning sensation, and other discomfort, resulting in decreased appetite of the patient.^[8]^ Feeding tube nutrition after laryngeal cancer plays an important role in the recovery of surgery and the improvement of patients’ quality of life, and the nursing of nasal feeding tube is an important part of perioperative nursing of laryngeal cancer patients.^[9,10]^ The conventional preoperative or intraoperative gastric tube placement depth is 40 to 55 cm, but the gastric tube placement depth makes most patients complain of chest and precardiac discomfort, such as stomach distension, cauterization, acid reflux, hiccup, and so on, which seriously affects the patient's tolerance and recovery.

The visual simulation scale can preliminarily judge the subjective feelings of patients. GCQ contains a total of 30 questions enrolling in 4 dimensions with 5 physical questions, 10 mental questions, 7 environmental questions, 8 social cultural questions; in addition, a total of 10 positive questions and 20 negative questions. Therefore, the simplified GCQ-Chinese translation has a high reliability and validity, which can reflect the comfort status of patients well and is applicable to all kinds of people.

This protocol aims at revealing the influence of 2 different gastric tube placement methods on postoperative comfort and prognosis of laryngeal cancer patients. This protocol may verify the rationality of an improved gastric tube placement method and has far-reaching clinical application significance for improving postoperative life quality and comfort of laryngeal cancer patients.

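### Every outcome in section 2.5 is designated primary and section 2.6 sets one P < .05 threshold, so no single result decides the trial and the chance of a false primary success is well above 5%

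*Protocol article*

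**What the plan says.** Section 2.5 (Measurement of outcomes) contains one list, introduced by "Tools to measure primary indicators include the following". It has three numbered entries:

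1. "The incidence of gastric complications".
2. Comfort, measured by a visual simulation scale and the general comfort questionnaire (GCQ), "including pain, acid reflux, upper abdominal burning sensation, and hiccup".
3. Prognosis, judged by "Objective indexes such as height, body mass index, albumin value, electrolyte, wound healing, and pharyngeal fistula". The words introducing the examples leave this entry open to further indexes.

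The article has no secondary list, singles out none of the entries, and gives no time point for any of them. Section 2.6 (Statistical analysis) gives one general rule: "Statistical significance will be considered at *P* < .05". The sample of 80 patients in section 2.2 is not linked to any one outcome.

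**The concern.** A primary outcome is meant to be the one result, or the few results under an explicit error rule, on which the trial's claim rests. Here the label covers every outcome in the article, and the same threshold is offered to all of them. Two consequences follow.

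- **False success.** With several chances at .05 each, at least one primary indicator can cross the threshold by chance far more often than one time in twenty. A report could then correctly say that a primary outcome was significant.
- **Conflicting results.** Section 2.1 aims at both comfort and prognosis. Comfort might improve while albumin falls, and the list does not say which finding would carry the conclusion.

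The choice of the deciding outcome would in effect be made after the data are seen.

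**Working it through.** The article states no familywise error rate and no power calculation, so there is no figure of its own to reproduce.

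**Inputs**

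- Per-test alpha: 0.05 (section 2.6). Sidedness is not stated; two-sided is assumed.
- Number of primary tests, k: not stated, so several counts from section 2.5 are used:
  - k = 3: one test per numbered entry.
  - k = 9: complications (1) + two comfort scales (2) + six named indexes (6).
  - k = 12: complications (1) + GCQ (1) + four symptoms scored separately (4) + six indexes (6).
- Correlation between test statistics: not stated; 0 to 0.7 is assumed, equal for all pairs.
- Tests: valid between-group comparisons are assumed.

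**Independent tests**

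P(at least one false positive) = 1 − (1 − 0.05)^k

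- k = 3: 1 − 0.95^3 = 0.143
- k = 9: 1 − 0.95^9 = 0.370
- k = 12: 1 − 0.95^12 = 0.460

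**Correlated tests**

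For equicorrelated normal test statistics with correlation ρ and two-sided 0.05:

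| k | ρ = 0 | ρ = 0.3 | ρ = 0.5 | ρ = 0.7 |
|---|---|---|---|---|
| 3 | 14.3% | 13.6% | 12.5% | 10.9% |
| 9 | 37.0% | 32.6% | 26.9% | 20.2% |
| 12 | 46.0% | 39.7% | 31.9% | 23.2% |

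The lowest entry, 10.9%, is still about twice the nominal 5%.

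**Height.** Leaving it out takes k from 9 to 8, and the independent figure from 37.0% to 33.7%. The conclusion does not change.

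**Limits of the calculation.** Section 2.6 describes the t test as comparing changes within groups, and some indicators (complications, fistula) are naturally binary. The figures therefore describe between-group tests that hold their level. Exact tests on rare binary events are conservative and would lower them somewhat. Separate within-arm tests would raise the number of tests.

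**After the fix**

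- One primary outcome tested at 0.05: 5%.
- Three co-primary outcomes, Bonferroni: 0.05 / 3 = 0.0167 each. If independent, 1 − (1 − 0.0167)^3 ≈ 0.049. The bound of 5% holds under any correlation.

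**The case against.** The strongest reply is that the text fixes less than the calculation supposes. Section 2.5 has three numbered entries, not twelve. The four symptoms may only describe what comfort covers, without being tested one by one. Section 2.6 gives a general threshold and does not say that each item is tested at .05 without adjustment. A multiplicity rule could stand in an analysis plan that is not shown.

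Most of this stands, but it bears on the size of the problem and not on its existence. The count of tests is uncertain, and item-by-item testing is inferred from the single threshold. An unseen analysis plan may well handle multiplicity. What cannot be put down to condensation is the designation: the article is not silent about which outcomes are primary, it names all of them. Even the reading with three tests and strong correlation gives about 11%.

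A reader might infer several stronger points that the documents do not support:

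- **That there are at least 12 primary tests, or that the false-success chance simply is 30–45%.** Twelve is one reading and not a minimum. That range needs roughly 7 to 12 tests with little or no correlation.
- **That the GCQ total would dilute any real effect**, because only 5 of its 30 items are physical (Discussion). This supposes that the GCQ total becomes the deciding outcome, which the article does not say, and that the other items would not respond. The Introduction attributes considerable psychological pressure to tube discomfort, and ten items are mental, so that assumption is undercut by the article itself.
- **That hiccup is counted twice.** The Discussion lists it among complications of prolonged tube placement in general, and section 2.5 lists it under comfort. The article does not define this trial's gastric complications, so double counting is possible but not shown.

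**Conclusion.** The concern holds as a defect of designation: all outcomes are primary, the list is open at its end, and one threshold applies with no stated order or division of alpha. Followed as written, a single significant indicator could not be read as confirmatory.

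The size depends on assumptions of this review. With no true effect and valid between-group tests, it runs from about 11% (three tests, correlation 0.7) to about 46% (twelve independent tests), with 20–37% for nine tests over the same range of correlation. Confidence is high that primary status is fixed badly and that the error rate exceeds 5%. It is much lower for any single percentage.

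**What to change.** Before any outcome data are analysed, amend sections 2.5 and 2.6 in one of two ways:

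- **One primary outcome.** Name one measure at one fixed postoperative time point, compared between groups at two-sided .05. The choice is the sponsor's; a comfort score or the incidence of gastric complications would both be defensible.
- **Three co-primary outcomes.** If all three groups are to stay primary, name one measure and one time point for each and share alpha: Bonferroni at .0167 each, or Holm.

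In either case, close the open-ended list and move the remaining indexes to secondary, reported as supportive. Report wound healing and pharyngeal fistula as safety outcomes with confidence intervals, so that possible harm stays visible whatever the significance tests show. Drop height as an outcome; it is not one that tube depth could plausibly change.

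The cost is rewording two short sections and updating the registry entry. The downside is that secondary outcomes can no longer carry a stand-alone claim of success. Under the co-primary option, each comparison also faces a stricter threshold with the same 80 patients.

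### Comfort, one of three groups of primary indicators, is self-rated, and no stated step shields the ratings from staff who can see the arm and expect the new position to help

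*Protocol article*

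**What the plan says.** Section 2.5 (Measurement of outcomes) lists three groups under primary indicators: gastric complications; comfort; and objective indexes such as body mass index, albumin, electrolytes, wound healing and pharyngeal fistula. For comfort, the visual scale and the GCQ "will be used to evaluate the comfort level of the 2 groups of patients, including pain, acid reflux, upper abdominal burning sensation, and hiccup". The Discussion confirms that this is self-report: "The visual simulation scale can preliminarily judge the subjective feelings of patients".

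Section 2.4 (Interventions) describes two procedures that look different to whoever carries them out. In the control arm the tube lies at 45 to 55 cm and gastric juice can be drawn. In the experimental arm "the gastric tube will be pulled out 10 cm after conventional placement and no gastric juice will be extracted". Ultrasound then confirms a different position in each arm.

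The Introduction reports the department's own experience: "we found that most patients have significantly reduced discomfort after 10 cm of gastric tube is removed". The trial is presented as a way of confirming that observation.

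Section 2.2 says patients are "randomly divided into control group and experimental group according to the numerical table". No section says what patients are told about the two positions, who hands out the questionnaires, or whether anyone is kept unaware of the arm.

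**The concern.** Three stated features combine. The outcome is the patient's own rating. Staff who handle the tube know the arm. The department running the trial has said which arm it expects to do better. A rating can then move in the expected direction without any real change in comfort, through what patients are told or through the manner in which the questionnaire is given and explained.

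Randomisation does not protect against this, because the shift arises after allocation. The analysis cannot remove it either: a reporting shift and a true comfort effect look the same in the data. At stake is whether a between-arm difference in comfort, if found, can be attributed to tube position.

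**Working it through.** **Does the text support each link?**

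| Link | Place | Status |
|---|---|---|
| Comfort is among the primary indicators | 2.5 | Stated, as one of three groups |
| Comfort is self-rated | 2.5, Discussion | Stated |
| Staff who place or aspirate the tube can tell the arm | 2.4 | Follows directly from juice versus none and the 10 cm withdrawal |
| The department expects benefit from withdrawal | Introduction | Stated |
| A step keeps tube-handling staff away from the ratings, or the expectation from patients | Nowhere in the article | None stated |
| Patients recognise their own arm | Nowhere in the article | Possible, not shown |

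**How large a shift would matter?**

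The plan gives no figure for reporting bias, so there is none to reproduce. The inputs are:
- Total 80, from section 2.2: "A total of 80 patients with laryngeal cancer in otolaryngology, head and neck surgery department". No allocation ratio is given; 40 per arm is assumed.
- Significance at P < .05, from section 2.6; two-sided is assumed.
- A between-arm t test is assumed. Section 2.6 does not clearly specify one: it says a t "test will be performed to compare the changes in measures within groups".
- No true effect, and a pure reporting shift of b standard deviations favouring the experimental arm. The size of b is an assumption, so a range is shown.

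Standard error of the difference in SD units: √(2/40) = 0.2236.

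Critical value: t(0.975; 78 df) = 1.991.

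Smallest observed difference that is significant: 1.991 × 0.2236 = 0.445 SD.

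Noncentrality: b / 0.2236 = b × √(40/2) = 4.472 b.

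P(significant in favour of experimental) = P(noncentral t with 78 df > 1.991).

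| Shift b (SD) | Noncentrality | Probability |
|---|---|---|
| 0 | 0 | 2.5% |
| 0.2 | 0.894 | 14.1% |
| 0.3 | 1.342 | 26.3% |
| 0.4 | 1.789 | 42.3% |
| 0.5 | 2.236 | 59.8% |

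For scale, the true difference detectable with 80% power under the same assumptions is about (1.960 + 0.842) × 0.2236 = 0.63 SD. A shift of 0.3 SD is roughly half of that.

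**The case against.** The strongest reply is that much of this rests on silence. The article is short, a full protocol may describe masking, and the article never calls the trial open label. That stands as far as it goes: a missing masking label would not be a finding by itself. What remains comes from the procedures, the outcome and the declared expectation, all of which are in the text.

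A reader might infer that patients know their arm. The documents do not support that. The Discussion describes conventional placement as before or during surgery, and section 2.4 does not say when the withdrawal takes place, so the patient may not be awake for it. Withdrawal from 45 to 55 cm leaves 35 to 45 cm, and a patient would have to read the mark and know what it means. Nothing says patients are told which position is expected to be better.

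A reader might also take comfort to be the main outcome and the trial's conclusion to be biased as a matter of course. Neither follows. Comfort is one of three groups of primary indicators, and the laboratory values and body mass index are hard to shift by expectation. Holding a hypothesis is normal in a trial and does not prove bias.

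The percentages are not evidence about this trial. They apply to any trial with 40 per arm and a shifted mean. Moreover, only 5 of the 30 GCQ items are physical, so a shift in symptom reporting need not carry over in full to the total score.

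**Conclusion.** The concern holds in limited form. As written, the comfort comparison is open to expectation bias toward the new position, because staff who know the arm belong to a department that expects benefit and no stated step separates them from the self-ratings. Symptom-based gastric complications are exposed to a lesser degree. Albumin, electrolytes and body mass index are largely unaffected.

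The documents do not show that bias will occur or how large it would be. If a shift of 0.2 to 0.5 SD did occur, the chance of a spurious significant result in favour of the experimental arm would rise from 2.5% to between about 14% and 60%. This rests on equal arms of 40, a two-sided between-arm t test and no true effect. The point should be dealt with before comfort data are collected, since it cannot be repaired at analysis.

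**What to change.** In sections 2.4 and 2.5:

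1. Tell patients that two tube positions are being compared, without naming their own position or the department's expectation.
2. Have patients complete the visual scale and GCQ in writing, away from staff who placed or handle the tube. Section 2.3 already excludes illiterate patients, so this is feasible.
3. Where existing staffing allows, have symptom-based gastric complications recorded against written criteria by staff who did not place the tube. This is secondary to items 1 and 2.
4. Ask patients at the last assessment to guess their arm, and report the answers by arm.
5. State that tube-handling staff are not masked and that comfort results are to be interpreted accordingly.

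Covering the external depth mark is not proposed, because it would touch the bedside check of tube position.

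The cost is wording in the protocol and patient information, plus one extra question. Items 1, 2, 4 and 5 add no procedure and no assessor. The drawback is that masking stays partial: staff who aspirate the tube can still recognise the arm, and some patients may learn theirs. If the full protocol already contains such steps, it is enough to state them here.
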